### Secondary Research Objectives

The **s**econdary research objectives were as follows:

Establish the participants’ expectancy toward both interventions.Examine the participants’ satisfaction with the interventions.Generate estimates to inform sample size calculations for a future multicenter RCT.Assess whether there is preliminary evidence of an efficacy signal for QoL, fatigue, symptoms, resiliency, self-efficacy, cognition, anxiety, depression, and mindfulness.Examine the experimental group’s baseline characteristics, adherence, and attrition rates in those who chose to continue for an additional 4 weeks compared with those who chose to complete the study at 4 weeks compared with those who were lost to follow-up.Examine the control group’s baseline characteristics, adherence, and attrition rates in those who chose to cross over to the experimental interventions at 4 weeks versus those who chose to complete the study at 4 week versus those who were lost to follow-up.Examine whether the experimental intervention is associated with differential brain-based imaging patterns of functional connectivity, cerebral blood flow, and spectroscopy.Examine safety by examining whether the experimental intervention has increased adverse events (ie, total number) relative to the control intervention.

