#### Control Group Description: Sham App

To control for daily access to the *AmDTx* platform, expectation, and clinical attention bias, we created a sham DTx for the control group. The sham DTx will be delivered on the same main interface, within *AmDTx*; however, these participants will not have access to any of the MBI training or psychoeducational content. Their sham DTx will consist of playing an open-source math game called 2048 developed by Gabriele Cirulli [44]; this will be communicated to the control participants as *cognitive training*. The game requires participants to slide number tiles on a grid and combine them to create a tile with the number 2048. In a previous study, *AmDTx* was compared with 2048, revealing that 2048 did not reduce stress or improve psychological well-being in university students with anxiety [27]. Furthermore, 2048 was previously tested in a pediatric population with concussion, and the study found no evidence of harm or symptom improvement at 4 weeks [45]. It is expected that the control intervention will not bother individuals with sensitivity to light or high velocity motion because it lacks fast visuals or movement. The game is programmed to only be accessible for 10 minutes per day.

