##### Safety

*Safety* of the MBI will be determined by capturing and monitoring the worsening of symptoms and adverse events. Adverse events will be defined as an unscheduled visit to the ED or primary medical provider because of exacerbation of symptoms during or within 30 minutes after using the app. The participant will be asked about any possible adverse events at the 1-, 2-, 4-, and 8-week follow-ups.

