#### Potential Harms

The safety outcomes include (1) severe worsening of symptoms identified on HBI reliable changes or (2) any symptoms requiring an unscheduled visit to the ED or primary care provider. If concussion symptoms worsen during the treatment to the degree that the participant requires an unscheduled visit to the ED or primary care provider, then symptoms will be considered as a possible adverse event. Symptoms could develop into an adverse event if they become unbearable and the patient needs immediate medical attention. Patients will report possible adverse events through REDCap reports, and their responses will be monitored by RAs. In the case of a possible adverse event, defined as the *worsening of symptoms requiring an unscheduled visit to the ED or primary care provider*, site investigators will be notified to determine if the event is linked to the treatment. If linked, the event will be monitored and the CHEO Research Ethics Board and DSMB will be notified.

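### The protocol gives two different scopes for a countable adverse event, one tied to 30 minutes after app use, and does not say which one the between-arm comparison uses

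*Protocol article*

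**What the plan says.** Four parts of the protocol article bear on this point.

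- **Secondary Research Objectives.** The safety objective is to examine "whether the experimental intervention has increased adverse events (ie, total number) relative to the control intervention".
- **Secondary Outcomes, Safety.** An adverse event is an "unscheduled visit to the ED or primary medical provider because of exacerbation of symptoms during or within 30 minutes after using the app". The same section says that safety is judged on symptom worsening as well as adverse events, and that participants are asked about possible adverse events at 1, 2, 4 and 8 weeks.
- **Potential Harms.** The safety outcomes are severe worsening shown by HBI reliable change, or "any symptoms requiring an unscheduled visit to the ED or primary care provider". A possible adverse event is symptom worsening that requires such a visit. Neither carries an app-use window. The site investigator then judges whether the event is linked to treatment: "If linked, the event will be monitored and the CHEO Research Ethics Board and DSMB will be notified".
- **Intervention descriptions.** For the control arm, "The game is programmed to only be accessible for 10 minutes per day". For the mindfulness arm the article recommends about 10 minutes a day on at least 4 days a week and states no upper limit.

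**The concern.** The objective is a count compared between arms, so the rule that admits an event to the count is part of the estimate. The article offers two rules of different breadth.

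The narrower rule, "during or within 30 minutes after using the app", builds a judgement about cause into the definition: worsening counts only if it comes close in time to app use. Worsening that builds up over days, or appears hours after a session, would not be an adverse event even if it brought the participant to the emergency department. The time during which an event can qualify is also set by how much the participant uses the app, which is itself a consequence of the assigned arm.

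At stake is how the safety statement carried into the efficacy trial can be read. A finding of no excess of adverse events, or of an excess, would depend partly on which definition was applied and on how the arms used the app.

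**Working it through.** The plan states no figure on this point that could be reproduced. The check is a comparison of the two sections, plus arithmetic to show how narrow the window is. I read the window as applying to the worsening, not to the visit.

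**Step 1. Apply both definitions to the same cases.**

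| Case | Safety section | Potential Harms section |
|---|---|---|
| Worsens during a session, unscheduled visit | Adverse event | Possible adverse event and safety outcome |
| Worsens overnight, hours after the last session, unscheduled visit | Not an adverse event | Possible adverse event and safety outcome |
| Same overnight case, judged not linked | Not an adverse event | Still a possible adverse event and safety outcome; event-level DSMB notice not triggered by this section |
| Severe HBI reliable worsening, no visit | Not an adverse event, though symptom worsening is monitored | Safety outcome, not a possible adverse event |

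The second and third rows are the conflict. The fourth shows that HBI worsening is a separate outcome in both sections and need not be merged into the event count.

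**Step 2. Ask which set the objective counts.** The objective refers only to adverse events and their total number. It does not say windowed or unwindowed, linked or all. The Safety section is the one place with a formal definition of the term, so an analyst could reasonably apply it and drop rows two and three.

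**Step 3. Width of the window.** Inputs: 10 minutes of use per session and 4 days a week (recommended minimum, experimental group description); 30 minutes after use (Safety section); 7 × 1,440 = 10,080 minutes in a week. One session per day of use is assumed.

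- Window per day of use: 10 + 30 = 40 minutes.
- At 4 days a week: 4 × 40 = 160 minutes; 160 / 10,080 = 1.6%.
- At 7 days a week: 7 × 40 = 280 minutes; 280 / 10,080 = 2.8%.

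These are shares of clock time. They would equal the share of worsening captured only if worsening were unrelated in time to app use, which the article does not tell us.

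**Step 4. Dependence on arm.** The window lengthens with app use. The sham game stops at 10 minutes a day. The mindfulness programme has no stated stop, and its Table 1 includes 15-minute body scans, for which the window would be 15 + 30 = 45 minutes against 40 for a single 10-minute game. Capture time can therefore differ by arm, but the article does not fix by how much or in which direction.

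**Step 5. Size of any undercount.** This needs the rate of unscheduled visits and their timing relative to app use. Neither is given, so no figure can be derived.

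**The case against.** The strongest reply is that the two sections use different terms. Potential Harms speaks of a possible adverse event that is then assessed, and the Safety section uses the same word for what participants are asked. On that reading the first is a screening term and the second the final definition. This is a fair reading, but nothing in the article states it. The only later filter in Potential Harms is linkage, not the 30-minute window, and unwindowed visits are listed there as safety outcomes in their own right.

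It can also be said that delayed worsening is not lost, because the HBI is taken at 1, 2, 4 and 8 weeks regardless of app use and its reliable worsening is a safety outcome. That stands: such worsening is measured, though it would not enter the count of adverse events.

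Three stronger readings are tempting, and the article does not support them.

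- A reader might infer that only linked events reach the DSMB. The Data Safety Monitoring Board section has the board told at once of severe adverse events, convened for a serious one, given interim safety results every year, and free to meet early on negative trends. None of this depends on linkage. Only the event-level notice in Potential Harms does. That notice is also an oversight route and does not decide which events enter the arm comparison.
- A reader might infer that the comparison is certainly undercounted. That follows only if the Safety definition governs the tally. The follow-up questions about possible adverse events carry no stated linkage or timing condition.
- A reader might infer that only mindfulness participants can have two sessions a day. The sham cap limits minutes, not sessions: two 5-minute games give 2 × (5 + 30) = 70 minutes, more than the 40 from one 10-minute session. The window also runs from use of the app, and controls use other features of it.

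Finally, safety is a secondary objective in a 70-participant feasibility trial and is not a progression criterion. That limits the consequence but does not settle which events are counted.

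**Conclusion.** The point holds as an unresolved conflict between the Safety and Potential Harms sections, which leaves the event set for the safety objective undefined. If the Safety definition is applied, visits for worsening outside the app window are excluded, and the window depends on app use that may differ between arms. The 1.6% and 2.8% figures show how narrow that window is at one 10-minute session per day of use; they do not estimate the number of events lost. The effect on the comparison could go in either direction.

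On oversight, a smaller point remains: event-level notice to the DSMB of a non-severe event depends on judged linkage, and the article does not say whether the annual interim safety results cover unlinked events. The matter should be corrected, but it does not threaten the feasibility objectives.

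**What to change.** Reconcile the two sections and name one event set for the safety objective.

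- **Count:** all unscheduled emergency department or primary-care visits for symptom worsening from randomisation to week 4, whatever their timing relative to app use and whatever the judged link. Stop at week 4 because controls are then offered the mindfulness programme, so later events no longer compare the randomised arms.
- **Alongside:** report HBI reliable worsening by arm as the separate safety outcome already named.
- **Attributes:** record for each event whether it arose during or within 30 minutes after app use, and the investigator's linkage judgement. Neither should act as a filter.
- **Oversight:** state that the interim safety results given to the DSMB include all such events, linked or not.

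The cost is definition wording and a longer event listing. Possible adverse events are already asked about at 1, 2 and 4 weeks, and the HBI is already collected. The article reports that data analysis has not yet been conducted, so the event set can still be fixed beforehand.

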##### Longitudinal Mental Well-Being

*AmDTx* contains 4 easy-to-use measurement features that together provide a longitudinal readout of patient well-being. First, psychological stress is objectively quantified via a 30-second *selfie* video that uses photoplethysmography to extract heart rate and 2 power bands of heart rate variability from biosignals inherent to the human face [79]. The amount of psychological stress is determined via a deep neural network trained on tens of thousands of selfie scans captured in parallel with a validated ecological momentary assessment of stress. The artificial intelligence output has reported 86% accuracy for determining an individual’s stress as *very low*, *medium low*, *medium high*, or *very high* [80]. Second, emotional affect and arousal levels are obtained via a digital 4-quadrant emotion mapping board (circumplex) that lists feelings such as *afraid*, *droopy*, and at ease ranging on one axis from unpleasant to pleasant (valence axis) and along another axis from mild to intense (arousal axis). Each emotion listed is associated with a score that is not disclosed to the user and is used to calculate an implicit measure of mood. Third, subjective stress is obtained via a slider ranging from *none* to *extreme*. Fourth, personal notes are imputed using an open field text box. The outputs of the mood and stress slider ecological momentary assessments have been benchmarked to standard psychological surveys [27]. If a participant chooses to use the selfie camera to observe their biological stress levels, there will be no recording or storage of the generated video in the app or elsewhere. The AmDTx uses secure web authentication, data logging, and encryption that ensure security and confidentiality of any personal identifiable information and in-app data. Personally identifiable information remains with the customer (ie, it is not downloaded by Mobio).

##### Imaging Measurements

*Imaging measurements* will be acquired within 72 hours of injury and during week 4 of the study on a subset of 60 participants. Each brain scanning session lasts 45 to 60 minutes and includes the following sequences: 3D T1-weighted anatomical scan to measure regional volumes and cortical thickness, resting-state functional MRI (rs-fMRI) to assess functional connectivity features or neural networks, arterial spin labeling to assess perfusion or cerebral blood flow, and magnetic proton spectroscopy in a single voxel in the anterior cingulate cortex to assess metabolite concentrations (ie, glutamate and gamma-aminobutyric acid). Table 3 lists the key imaging parameters.

#### Covariate Measurements

Information about injuries will be collected from medical records and medical personnel using a standardized case report form. Details regarding the injury and acute signs and symptoms of concussion (ie, loss of consciousness, Glasgow Coma Scale scores, mechanism of injury, neurological status, and other clinical features) will be collected by RAs, with clarification by physicians when necessary. The data will be verified by the site investigator. To calculate the 5P clinical risk score [2], balance will be evaluated by the RA using the balance error scoring system [81], a widely used instrument in the field of sports concussion [82] for objective assessment of postural stability. Pubertal status will be measured using a puberty questionnaire [83]. The questionnaire is a 5-item, self-administered rating scale for pubertal development without pictorial representations or interviews. Demographic data (ie, household annual income and parental education level) will be used as a proxy of socioeconomic status (SES). SES will be collected to assess whether randomization is equally distributed in both groups. If SES is not equally represented in the sample, it will be controlled for in our analysis.

Studies have shown that physical activity can reduce anxiety, improve mood, and help alleviate postconcussive symptoms [84]. We will evaluate physical activity to ensure balance between groups; physical activity levels will be assessed using the Godin-Shepard Leisure-Time Physical Activity Questionnaire [85] on day 1 and then at 2, 4, and 8 weeks after injury.

### Procedures

#### Data Collection Methods

Recruitment will be conducted similar to the successful Pediatric Concussion Assessment of Rest and Exertion multicenter concussion study [86]. When an adolescent with a mechanism of injury and symptoms consistent with concussion presents to the ED, the nurse will triage the child as per the existing protocols. Once in the ED, a member of the ED clinical team (ie, an ED volunteer) will introduce the study to families of potentially eligible children to inquire whether they are interested in learning more about the study. If so, the electronic charts of potentially eligible participants will be flagged, and the research team will be notified. At 360cc, a health information custodian who is a part of the circle of care will mention to the family that there is a study on children who have head injuries and ask if they are interested in learning more about the study. In both the ED and 360cc, the RA will then approach the family to discuss the research study, and if they are interested, the RA will complete the screening form on an iPad.

During the screening procedure, we will evaluate the likelihood that the patients had a *definitive* or *probable* concussion based on the aforementioned inclusion criteria. Their 5P clinical risk score [2] will also be calculated with the following variables: age, sex, prior concussion and length of recovery, history of migraine, slow answers to questions, balance, headache, sensitivity to noise, and feeling fatigued. Only patients with a 5P score >4 will be eligible for the study. Patients who are ineligible based on the initial screening will be thanked for their time. Eligible and willing parents along with adolescents capable of consenting on their own behalf will be asked for written informed consent, and the adolescents who are unable to provide consent on their own behalf will be asked for assent.

Once enrolled in the study, the families will complete a series of questionnaires in an electronic survey format using a portable tablet computer on REDCap [87]. The survey includes questions regarding patient demographics, preinjury and injury characteristics, a symptoms checklist, and diagnostic history.

The day following the ED or 360cc visit, participants will receive a phone call from an RA to randomize the participants to either the experimental or the control group and give instructions to register an account on a study-dedicated landing page using a unique link for each participant. Following registration, participants will install *AmDTx* on the mobile device of their choice. After creating an account and logging in to *AmDTx*, each participant will be automatically directed to their assigned intervention (MBI or control).

During this phone call, an MRI appointment will be scheduled for the participants who have agreed to participate in that component of the study. Participants will complete the surveys or questionnaires for day 1 and MRI screener. They will have the option of completing the survey via phone or REDCap.

#### Follow-Up Procedures

The proposed duration of the app-based MBI is 4 to 8 weeks. After 4 weeks, all participants in the experimental group will be given the opportunity to pursue the MBI for an additional 4 weeks. At that time, participants in the control group will be offered to cross over and start the MBI intervention.

Participants will complete electronic follow-up questionnaires on REDCap at 1, 2, 4, and 8 weeks after enrollment and will have an in-person follow-up at 4 weeks for the cognitive assessment (and the MRI scan for a subset of participants). Cognitive testing will be conducted before brain scanning.

#### Neuroimaging Procedures

A subset of 60 participants (30 from each group) will undergo a 45-minute MRI scan at <72 hours and 4 weeks after injury. During the day 1 phone call, participants who have consented to the MRI component of the study will complete the MRI screener and schedule their MRI appointment.

Each scanning session will be approximately 1 hour and will include a high-resolution structural scan, arterial spin labeling, rs-fMRI, and magnetic proton spectroscopy (Table 4).

**Table 4 table4:** Magnetic resonance imaging acquisition.

Image type	Sequence name	Total time (minutes:seconds)	Resolution (mm×mm×mm)	Slices, n	FOV^a^ (mm)	TR^b^ (milliseconds)	TE^c^ (milliseconds)	Other
High-resolution anatomical	MEMPRAGE	5:48	1.0**×**1.0**×**1.0	192	256	2500	1.69, 3.55, 5.41, and 7.27	Flip angle=7; inversion time=1050 milliseconds; phase FOV=100%
rs-fMRI^d^	—^e^	12:08	3.0**×**3.0**×**3.0	40	204	2160	25	Flip angle=70; acceleration factor=2; 334 volumes
ASL^f^	3D ASL (GRACE)	5:37	1.8**×**1.8**×**5.0	34	230	4600	15.56	Perfusion mode=Flow-sensitive Alternating Inversion Recovery-QII; bolus duration=700 milliseconds; inversion time=860 milliseconds, 1060 milliseconds, 1260 milliseconds, 1460 milliseconds, 1660 milliseconds, 1860 milliseconds, 2060 milliseconds, 2260 milliseconds, 2460 milliseconds, 2660 milliseconds, 2860 milliseconds, 3060 milliseconds; average=1
ASL	Calibration image (M0)	0:54	1.8**×**1.8**×**5.0	34	230	7500	15.92	Perfusion mode=Flow-sensitive Alternating Inversion Recovery-QII; bolus duration=700; inversion time=7000 milliseconds; average=1
MRS^g^	PRESS	4:38	40**×**20**×**15	—	—	2000	30	Average=128
MRS	MEGAPRESS	4:36 (×2)	40**×**20**×**15	—	—	2000	68	Average=64

^a^FOV: field of view.

^b^TR: repetition time.

^c^TE: echo time.

^d^rs-fMRI: resting-state functional magnetic resonance imaging.

^e^Not available.

^f^ASL: arterial spin labeling.

^g^MRS: magnetic resonance spectroscopy.

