## Methods

### Trial Design

The proposed study is a Health Canada–regulated parallel-group (1:1) RCT, where patients within 7 days of a concussion will be randomly assigned to one of the two groups: (1) experimental group (n=35), early introduction of the DTx MBI program and (2) control group (n=35), sham DTx attention-matched comparator intervention. The participants will start the intervention the next day after being enrolled in the study. After 4 weeks, those in the experimental group will be offered the MBI program with 4-week additional education modules. Those who are part of the control group will be offered to cross over to start the DTx MBI. Of the 70 participants enrolled, 60 (86%) consenting participants (n=30, 50% from the experimental group and n=30, 50% from the control group) will be enrolled in neuroimaging, which requires participation in a brain scanning session within 72 hours of enrollment and during week 4 of the study. For a schematic diagram of the trial design, procedures, and stages, refer to the study flow diagram in Figure 1.

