#### Exclusion Criteria

Patients will be excluded if they present with TBIs with any of the following: (1) a Glasgow Coma Scale score of ≤13; (2) abnormality on standard neuroimaging studies [41], including positive head computed tomography findings (neuroimaging is not required, but may be performed if clinically indicated); (3) neurosurgical operative intervention, intubation, or intensive care required; (4) multisystem injuries with the treatment requiring hospital admission, operating room, or procedural sedation in ED (hospital admission for observation or management of ongoing concussion symptoms is not an exclusion criteria); (5) severe chronic neurological developmental delay resulting in communication difficulties; (6) intoxication to alcohol or drugs at the time of ED presentation as per clinician judgment; (7) no clear history of trauma as primary event to the concussion (eg, seizure, syncope, and migraine); (8) prior psychiatric hospitalization; (9) inability to obtain written informed consent or assent (eg, language barrier); (10) legal guardian not present (certain forms need to be completed by parents or legal guardians); (11) no internet and mobile or tablet access; and (12) currently in therapy.

In addition, patients will not be included in the magnetic resonance imaging (MRI) component if they present with the following: (1) previous neurological or neurodevelopmental disorder such as epilepsy, intellectual disability, or autism (history of attention-deficit or hyperactivity disorder or learning disability is not exclusionary); (2) previous stroke or transient ischemic attacks; (3) sedation medication (eg, propofol, ketamine, nitrous oxide, midazolam, benzodiazepines, and fentanyl) administered before or during ED visit; (4) inability to be present at the 72-hour (+48 or –48 hours) and 4-week (+5 or –5 days) MRI follow-up visits; and (5) medical contraindications to MRI (eg, claustrophobia, pregnancy, or presence of braces or spacers or other metal implants).

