#### Implementation

The day after enrollment and once all questionnaire data are complete, research assistants (RAs) will call participants over the phone, and RAs will log into REDCap (Research Electronic Data Capture; Vanderbilt University) to obtain the patient’s group allocation. Only the RAs who randomized participants will be unblinded. The research team will be blinded to data acquisition. In case of a serious adverse event, the principal investigator and appropriate research staff will be unblinded to the participant’s group.

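### MRI screening and booking share the call that opens the allocation, and the subset is set at 30 per arm without stratifying for it, so entry to the imaging comparison can depend on arm

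*Protocol article*

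**What the plan says.** All references are to the protocol article.

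- **The call.** Under Data Collection Methods, on the day after the visit "participants will receive a phone call from an RA to randomize the participants to either the experimental or the control group" and to explain how to set up the app. The next paragraph adds: "During this phone call, an MRI appointment will be scheduled for the participants who have agreed to participate in that component of the study". It also has participants complete the day-1 questionnaires and the MRI screener, and "They will have the option of completing the survey via phone or REDCap".
- **The screener.** Neuroimaging Procedures gives the same timing: "During the day 1 phone call, participants who have consented to the MRI component of the study will complete the MRI screener and schedule their" scan.
- **Who knows the arm.** Under Implementation, the RA takes the allocation from REDCap on the day after enrolment, when the questionnaire data are finished. The section adds: "Only the RAs who randomized participants will be unblinded".
- **MRI exclusions.** Exclusion Criteria lists five that apply to the MRI component only. One is "inability to be present at the 72-hour (+48 or –48 hours) and 4-week (+5 or –5 days) MRI follow-up visits". Another covers medical contraindications, with claustrophobia among the examples.
- **Numbers.** Trial Design sets the subset of 60 as "n=30, 50% from the experimental group and n=30, 50% from the control group". Neuroimaging Procedures and the sample-size section for the nested component repeat 30 per group.
- **Stratification.** Sequence Generation stratifies by sex only.

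**The concern.** The imaging question, as put in the Abstract and the secondary objectives, is whether adolescents randomised to the mindfulness app differ on MRI from those randomised to the sham app. That comparison is protected only if entry to the MRI subset cannot be influenced by the arm. Two features of the plan leave a route for influence.

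First, screening and booking sit in the call that opens the allocation, handled by someone who knows the arm or learns it during that call. Whether a family can attend two scan visits depends partly on the effort put into finding a slot, and claustrophobia depends on self-report. Either could vary with arm once the arm is known.

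Second, a fixed 30 per arm does not follow from a randomisation that ignores MRI participation. Holding to it may mean accepting or declining people by arm. The planned regression adjusts for age, sex, handedness (for resting-state fMRI) and potential confounders on which the groups differ at baseline. It cannot correct selection on factors that were not measured.

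**Working it through.** **1. The plan's own figure.** The base of 24 comes from a cited source and cannot be derived from the article. Doubling for multiple comparisons gives 24 × 2 = 48. Allowing for 20% attrition gives 48 / (1 − 0.20) = 60, or 30 per group. The stated number reproduces, and it is derived as a sample-size target.

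**2. Order of steps.** Three statements bear on this.

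- Data Collection Methods names randomisation first, runs on to app installation, then returns to the same call for MRI booking, the questionnaires and the screener.
- Neuroimaging Procedures puts screener and booking in that call.
- Implementation makes the allocation wait for the questionnaire data. It does not name the MRI screener, and it fits poorly with day-1 questionnaires that are themselves completed at or around the call.

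Taken together, the order of screener and allocation is open. No sentence closes it.

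**3. Chance of an even split.** Inputs: 35 randomised per arm and 60 MRI participants (Trial Design). Assume that exactly 60 of the 70 are MRI-eligible and that eligibility is unrelated to arm. The number in one arm is then hypergeometric:

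P(30/30) = C(35,30)² / C(70,60) = 324,632² / 396,704,524,216 = 0.266.

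| Split | Probability |
|---|---|
| 30/30 | 26.6% |
| 31/29 | 42.8% |
| 32/28 or more uneven | 30.6% |

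**4. How often a cap of 30 would bind.** Let p be the share of randomised participants who consent to MRI and pass its criteria. The article does not give p, so the values below are assumptions. With X ~ Binomial(35, p) in each arm independently and b = P(X ≥ 31):

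P(at least one arm exceeds 30) = 1 − (1 − b)².

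P(both arms reach 30) = P(X ≥ 30)².

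| Assumed p | b | At least one arm exceeds 30 | Both arms reach 30 |
|---|---|---|---|
| 70% | 0.009 | 2% | 0.1% |
| 80% | 0.144 | 27% | 7% |
| 85.7% (= 60/70) | 0.427 | 67% | 38% |
| 90% | 0.731 | 93% | 75% |

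Example at 80%: 1 − (1 − 0.1435)² = 1 − 0.7336 = 0.27.

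The middle column is the chance that holding to 30 would decline someone because of their arm. At the lower rates the more likely outcome is a shortfall, because 30 of 35 needs 86% of each arm.

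**The case against.** The case on the other side has real content.

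- **MRI consent precedes the call.** Both procedural sections speak of participants who have already agreed. Only screening, booking and the per-arm number are exposed. This stands.
- **Who judges the screener is not stated.** A reader might infer that the unblinded RA decides MRI eligibility. The article says that participants complete the screener, and the option of phone or REDCap leaves room for self-completion. It does not support more than that the call and booking are handled by an RA who is or becomes unblinded.
- **The text may not be chronological.** A reader might infer from the order of the sentences that the arm is already known at screening. The account goes back to the same call after describing app set-up, so this does not follow. What stands is that no order is fixed.
- **No closing rule is written.** Thirty per arm is a target. Declining people by arm would follow from holding to it; it is not an instruction in the plan.
- **The split figures can be over-read.** A reader might infer that in the remaining 73% of trials 30 + 30 could be reached only by refusing people by arm. It could not be reached that way. With exactly 60 eligible, a 31/29 split cut back by refusal gives 30/29. The cap calculation is the relevant measure of refusal by arm.
- **The room for bias is limited.** Most MRI exclusions are history or hard contraindications, and families are blinded to the purpose and to the other arm.
- **The imaging analysis is per protocol.** Restricting to adherers departs from the randomised comparison anyway. A reader might infer that the screening order is what breaks it, or that correcting the order would restore it. Neither follows.

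The order of steps within a call could also be called detail for the full protocol. But the article itself states the shared call and the per-arm number, and those are what the point rests on.

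**Conclusion.** The point holds as a route by which MRI entry can depend on arm. It does not show that entry will depend on arm, and no size of bias can be derived from the article. It rests on three stated facts: screener and booking in the randomising call, 30 per arm, and stratification by sex only. It also rests on the absence of any requirement that MRI eligibility be fixed before allocation is opened.

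An exact 30/30 split is unlikely to arise by itself: 26.6% if exactly 60 are eligible, although a further 42.8% would be a trivial 31/29. The chance that a cap of 30 would act by arm runs from about 2% to 93% over assumed rates of 70% to 90%. These figures assume 35 randomised per arm and MRI eligibility unrelated to arm.

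The scope is the nested secondary imaging comparison. The primary feasibility outcomes are untouched, and the per-protocol restriction is a separate matter that this does not cure. This is a cheap improvement.

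**What to change.** 1. Complete the MRI screener and the check on availability for both scan visits before allocation is opened, either at the enrolment visit or as the first step of the day-1 call.
2. Lock an MRI-eligible yes/no flag in REDCap, and make the allocation accessible only once it is set.
3. Replace the per-group number with up to 60 MRI-eligible participants in total, in whatever split randomisation gives.
4. Align the wording of Implementation with Data Collection Methods on what must be complete before the RA obtains the allocation.
5. Recruitment began in October 2022, so for participants already randomised report by arm the numbers who consented to MRI, were screened, were excluded (with reason) and were scanned.

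The cost is a form moved slightly earlier, one REDCap gate and one extra table. The downside is that the MRI arms may be slightly uneven.
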